#### TB/HIV indicators

In each community TB/HIV programme indicators as described in the WHO guide to Monitoring and Evaluation of TB/HIV collaborative Activities [14] will be collected throughout the study period. These will provide the secondary outcome measurements at community level.

### Sample size

Based on data from prevalence studies in Cape Town [15] and WHO estimates of tuberculosis prevalence[16] we assumed a prevalence of tuberculosis in the control arm of 1%. We powered our study in order to be able to detect a 30% reduction in prevalence of tuberculosis due to each intervention individually and a further 30% reduction in tuberculosis prevalence when the two interventions are combined. To achieve 80% power of detecting a significant difference (2-sided p < 0.05), an assumed between-community coefficient of variation *k *= 0.20 and 5,000 individuals sampled per community (Tab 1 and figure 2) we would need 12 communities in each arm. The total sample size will therefore be 24 communities, 6 in each of the four arms[17].

**Table 1 T1:** Sample size calculations for power of 80% (two-sided, 5% significance level), based on sample of 5000 individuals per community and allowing for 20% losses, for each of the main comparisons (ECF vs non-ECF & HH vs non-HH)

Prevalence (%) in Control arm	Reduction in Prevalence due to each intervention (ECF or HH) individually	Prevalence (%) in ECF or HH arm	Overall number of communities needed (equally split into 4 arms)
**k = 0.15**			

0.6	30%	0.42	24
0.8	30%	0.56	20
1.0	30%	0.7	18
1.0	20%	0.8	41
1.0	10%	0.9	168

**k = 0.2**			

0.6	30%	0.42	30
0.8	30%	0.56	26
1.0	30%	0.7	24
1.0	20%	0.8	54
1.0	10%	0.9	227

**k = 0.25**			

0.6	30%	0.42	45
0.8	30%	0.56	42
1.0	30%	0.7	39
1.0	20%	0.8	93
1.0	10%	0.9	398

k = between-cluster coefficient of variation

**Figure 2 F2:**
[figure not shown]
Graph showing the effects on sample size of different inter-cluster coefficients of variation (k).

The two primary study questions will be answered by comparing 12 communities with the other 12 (e.g. non-ECF arms 1 & 3 Vs. ECF arms 2 & 4 or non-HH arms 1 & 2 Vs. HH arms 3 & 4), allowing for the factorial design this means that we assume a TB prevalence of 1% in the control arm (arm1), 0.7% in single intervention arms (arm 2 and arm 3) and 0.49% in the arm with both interventions (arm 4). Overall, the primary study comparisons will therefore be able to detect the 30% reduction in TB prevalence from 0.85% to 0.595%.

For the secondary outcome of cumulative incidence of tuberculosis infection over three years of intervention, as measured by TSTs, we wish to detect a 30% reduction associated with either the ECF or HH intervention. The sample size is calculated to provide 80% power of detecting this difference (two-sided p < 0.05,) on the assumption that there will be 12 communities in each of the arms for the two main comparisons and with *k *= 0.20. Under these assumptions, and with an assumed 3% cumulative incidence of tuberculosis infection over three years (at 1% annual risk of infection) in the control arm and allowance for 20% loss to follow-up, we will need to initially recruit 800 children in each community.

HIV incidence will be measured in the secondary outcome cohort of 150 TB patients and their households per community. Each household would be expected to include 2–3 HIV negative adults at the start of the study. Allowing for loss to follow-up of 20%, this sample size will provide 80% power to detect a reduction in cumulative HIV incidence of 40%, (2-sided p <0.05)) assuming HIV incidence in those individuals not receiving the intervention is at least 0.7% per year (cumulative incidence 2.1% over 3 years).

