### Design of the randomised trial

The interventions are being evaluated by means of a 2 × 2 factorial community randomised trial.

The primary study questions are:

• Does enhanced tuberculosis case finding (ECF), by a strategy of community mobilisation and enhanced access to sputum microscopy, reduce prevalence of tuberculosis in the community?

• Does a strategy of combined TB/HIV activities at the household level (HH), that includes active case-finding, isoniazid preventive therapy, and psychosocial and adherence support for both treatment and prevention of tuberculosis and HIV, reduce prevalence of tuberculosis in the community?

The unit of randomisation will be the population accessing one TB diagnostic centre (which will be known as the "community"). A 2 × 2 factorial design will be used so that there will be four arms:

Arm 1: Standard TB/HIV Control activities at the clinic only

Arm 2: Standard TB/HIV Control activities at the clinic *plus *ECF

Arm 3: Standard TB/HIV Control activities at the clinic *plus *HH

Arm 4: Standard TB/HIV Control activities at the clinic *plus *ECF *plus *HH

The primary analysis will be a comparison of ECF Vs no ECF (arms 2 & 4 vs arms 1 & 3) and of HH Vs no HH (arms 3 & 4 vs arms 1 & 2). This allows the questions posed in the specific objectives to be addressed. The factorial design will also allow arm 4 to be compared directly to arm 1, referred to as the control arm in this paper, to address the question:

• What is the overall effect of the combined interventions (ECF+HH) on the prevalence of tuberculosis in the community?

A cohort of consecutive TB patients and their households in each community will be followed for the duration of the interventions to allow analysis of household-level outcomes, using both epidemiological and social science methods.

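### Table 1 is captioned as sizing the two main comparisons, but its columns, and apparently its totals, use arm 1 against a single-intervention arm (1.0% v 0.7%) instead of the factorial margins (0.85% v 0.595%); 24 communities still suffice

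*Protocol article*

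**What the plan says.** All references are to the protocol article.

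- **Design of the randomised trial.** The primary analysis compares arms 2 and 4 with arms 1 and 3 (ECF), and arms 3 and 4 with arms 1 and 2 (HH). Arm 1 is "referred to as the control arm in this paper".
- **Sample size, opening paragraph.** "we assumed a prevalence of tuberculosis in the control arm of 1" per cent. The aim is to "detect a 30% reduction in prevalence of tuberculosis due to each intervention individually". With 80% power, two-sided 5% significance, k = 0.20 and "5,000 individuals sampled per community", the result is 12 communities on each side of a comparison, 24 in all.
- **Table 1, caption.** The totals are described as "allowing for 20% losses, for each of the main comparisons (ECF vs non-ECF & HH vs non-HH").
- **Table 1, columns.** These are the prevalence in the control arm (0.6, 0.8 or 1.0% in the 30% rows), the reduction from each intervention individually, and the prevalence in the ECF or HH arm (0.42, 0.56 or 0.7%). At k = 0.20 the printed totals for these rows are 30, 26 and 24.
- **Sample size, text after Figure 2.** The arm prevalences are set at 1% (arm 1), 0.7% (arms 2 and 3) and 0.49% (arm 4). The conclusion follows: "Overall, the primary study comparisons will therefore be able to detect the 30% reduction in TB prevalence from 0.85% to 0.595" per cent.

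**The concern.** The caption and the columns of Table 1 describe different contrasts. The caption names the main comparisons, which are differences between factorial margins. The columns hold the arm 1 prevalence and the prevalence the text gives to a single-intervention arm. Half of the communities on each side of a main comparison also receive the other intervention, so both sides have lower prevalence than the columns show. The relative reduction stays at 30%, but fewer cases are counted and sampling error is larger in relative terms.

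The table itself points to the gap. If its rows are direct two-group contrasts, 0.8% v 0.56% needs 26 communities and 1.0% v 0.7% needs 24. A contrast of 0.85% v 0.595% lies between them and should need more than 24 by the same method.

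Two things are at stake: whether the stated 80% is the power of the primary comparison, and whether the lower-prevalence rows are a fair guide to robustness.

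**Working it through.** **Inputs.** Two-sided 5% significance, 80% power, k = 0.20, 5,000 sampled per community, 20% losses (so 4,000 evaluable), arm 1 at 1.0%, and a 30% reduction per intervention. All come from the Sample size section and Table 1.

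**Formula (inferred; the article does not print one).** Standard unmatched cluster formula, communities per side:

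c = 1 + 7.849 × [p0(1−p0)/n + p1(1−p1)/n + k²(p0² + p1²)] / (p0 − p1)², total = 2c.

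**Step 1. Reproduce the printed 24 (1.0% v 0.7%, n = 4,000, k = 0.20).**
- Bracket: 2.475 + 1.738 + 5.960 = 10.173 (×10⁻⁶). Squared difference: 9.000 (×10⁻⁶).
- c = 1 + 7.849 × 10.173/9.000 = 9.87, so 2c = 19.74. Multiplied by 1.2 this is 23.69; printed 24.

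**Step 2. Test the reconstruction on the other rows** (order: 0.6%, 0.8% and 1.0% with 30%; then 1.0% with 20% and 10%).

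| Block | Printed | Column contrast, n = 4,000, ×1.2 | Margins, n = 5,000, ÷0.8 |
|---|---|---|---|
| k = 0.15 | 24, 20, 18, 41, 168 | 24.16, 20.46, 18.23, 40.78, 167.74 | 24.28, 20.65, 18.47, 40.06, 160.19 |
| k = 0.20 | 30, 26, 24, 54, 227 | 29.62, 25.92, 23.69, 54.29, 227.41 | 29.96, 26.33, 24.15, 54.14, 222.34 |

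The column contrast matches all ten totals to the nearest integer. The last column is the most plausible way in which the dilution could already be included. It fits most 30% rows but gives 160 for 168 and 222 for 227, which is not rounding. The block labelled k = 0.25 matches the column contrast only if k = 0.30 is entered (45.22, 41.51, 39.29, 92.91, 397.88; printed 45, 42, 39, 93, 398). That is a separate matter.

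**Step 3. Factorial margins for a 30% effect.** Without the intervention: (1.0 + 0.7)/2 = 0.85%. With it: (0.7 + 0.49)/2 = 0.595%. In general these are arm 1 × 0.85 and arm 1 × 0.595.

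**Step 4. Main comparison (0.85% v 0.595%, n = 4,000, k = 0.20).**
- Bracket: 2.107 + 1.479 + 4.306 = 7.892 (×10⁻⁶). Squared difference: 6.5025 (×10⁻⁶).
- c = 1 + 7.849 × 7.892/6.5025 = 10.53, so 2c = 21.05; ×1.2 = 25.26.

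| Arm 1 | Margins | Printed total | Margins, table's apparent method | Margins, one loss allowance | Power, 12 v 12 |
|---|---|---|---|---|---|
| 1.0% | 0.85 v 0.595% | 24 | 25.3 | 21.1 | 85% |
| 0.8% | 0.68 v 0.476% | 26 | 27.9 | 23.2 | 81% |
| 0.6% | 0.51 v 0.357% | 30 | 32.2 | 26.9 | 75% |

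**Step 5. Power.** Power = Φ(√[(c − 1)(p0 − p1)²/bracket] − 1.96). At 1.0% with c = 12: √(11 × 6.5025/7.892) = 3.011, and Φ(1.051) = 0.853. The same formula on the column contrast gives 88%, 84% and 79%. With a t distribution on the 16 df named in the Analytic plan, the main comparison has 84%.

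**The case against.** The strongest reply is that nothing in the design is wrong. With the one 20% allowance that the caption describes, the margins need 21.1 communities, which becomes 24 in four equal arms, and 12 v 12 gives more than the planned 80%. The sentence about 0.85% v 0.595% is therefore true as a statement of what the trial can detect. The article also sets out all four arm prevalences and derives the margins openly, so a reader knows which contrast is primary. The printed 0.6% row already asks for 30 communities, which warns that 24 falls short there. All of this stands.

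A reader might infer that every total in Table 1 is too low, or that 24 does not follow. The documents do not support either reading. With one loss allowance, every printed total exceeds its marginal requirement: at k = 0.20 the requirements are 26.9, 23.2, 21.1, 47.2 and 193.4, against 30, 26, 24, 54 and 227. At k = 0.15 they are 22.3, 18.7, 16.5, 35.9 and 143.7, against 24, 20, 18, 41 and 168. The block labelled k = 0.25 is too high at its label even with the extra 1.2 (margins 39.3, 34.9, 32.3, 74.0 and 308.8; printed 45, 42, 39, 93 and 398). The totals look low only if that extra factor is kept.

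It could also be said that control arm in Table 1 loosely means the non-intervention side. The article defines the term as arm 1, and the text gives the 1% to arm 1. Even on the loose reading, the 1.0% row is not the row for 0.85%.

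The reply does not remove the mismatch itself: the table is captioned for one contrast and evidently computed on another.

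**Conclusion.** The point holds as an error of derivation and labelling in the primary sample-size table. It is not evidence of an underpowered trial. The change of contrast alone moves the chosen row from 19.7 to 21.1 communities with one loss allowance, or from 23.7 to 25.3 by the table's apparent method. The result is still 24 because the totals appear to allow for losses twice, once through 4,000 evaluable and once through the factor of 1.2, and this more than offsets the missing dilution. The stated 80% is therefore not the power of the primary comparison, which is about 85% at the planned inputs. Robustness at lower prevalence is slightly worse than the same formula gives on the printed contrast: 81% rather than 84% at 0.8%, and 75% rather than 79% at 0.6%.

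This rests on the inferred formula, on k = 0.20 applying to the main comparisons, on 4,000 evaluable per community, on a normal approximation, on independent 30% effects, and on the other intervention's effect not adding to the residual variation. The disagreement between caption and columns does not depend on the reconstruction.

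**What to change.** Recompute Table 1 on the factorial margins with a single 20% loss allowance. For a 30% effect these are arm 1 × 0.85 v arm 1 × 0.595, with the corresponding margins for the 20% and 10% rows. Head the columns as prevalence in non-ECF (or non-HH) communities and in ECF (or HH) communities, keep the arm 1 prevalence as a separate column, and state the formula.

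Replace the sentence after Figure 2 with wording such as: With 24 communities (6 per arm), k = 0.20 and 4,000 evaluable adults per community, each main comparison has about 85% power (normal approximation) to detect 0.85% v 0.595%, about 81% if arm 1 prevalence is 0.8%, and about 75% if it is 0.6%.

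The cost is one recalculated table and one sentence. No communities are added and the analysis is unchanged. The only loss is that the robustness figures at lower prevalence read a little less favourably.

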### Randomization

Due to the small number of communities in the study we stratified randomisation by country and the prevalence of TB infection (as measured by baseline TST surveys and categorised as high/low within countries). We used restricted randomisation to ensure balance on TST prevalence, HIV prevalence, urban/rural, social context and geographical location. A two-stage public randomisation ceremony was conducted to select one of the possible allocations for the study arms and then to allocate the interventions to those study arms. The design and results of this allocation procedure have been described in another paper [18].

### Analytic plan

As a community randomised trial ZAMSTAR will be analysed both at the cluster level, by deriving summary statistics for each community, and at the individual level using data from each individual in each community. For these analyses statistical methods that take account of between- and within-cluster variation will be used. The analysis will give each community equal weight. There are three intervention comparisons that will be made assessing the effects of ECF alone (12 Vs 12 communities), HH alone (12 Vs 12 communities) and ECF plus HH combined (6 Vs 6 communities). Impact measures of the above comparisons will be based on ratios.

To account for the study design, suitable generalized linear models will be used, where appropriate, to allow for clustering by community. For the binary outcomes (prevalence, incidence) the overall risk/rate for each cluster will be calculated. Risks/rates for each cluster will be shown, by strata and arm. A log transformation to normalise data will be applied to the risk/rate for each cluster. The mean and SD of these log risks/rates will be used to obtain the geometric mean (if the log transformation is clearly inappropriate the arithmetic mean will be used instead) and associated 95% CI for each intervention arm of the study. Linear regression of the log mean risk/rate on strata and arm will be used to estimate the relative risk/rate and 95% CI associated with the intervention. The approximate variance for the mean risks/rates ratio is obtained based on the residual mean square from a two-way analysis of variance (ANOVA) of community log-risk on stratum and study arm. A 95% CI for the relative risk/rate will be calculated from this variance using a t-statistic with 16 degrees of freedom (df) for the two main comparisons and 10 df for the comparison of arm 4 Vs arm 1.

For the continuous outcomes such as intervention costs and stigma levels, the overall mean for each community will be calculated, and means for each community will be shown, by strata and arm. The arithmetic mean and SD of these mean scores/numbers and associated 95% CI for each intervention arm of the study will be calculated. Linear regression of the mean score/number on strata and arm (2-way ANOVA on intervention and strata) will be used to estimate the difference in score/number and 95% CI associated with the intervention.

Apart from calculation of crude effects, adjusted analyses to account for potential confounding effects will also be performed. Potential confounding factors will include age, sex, TB infection prevalence (as calculated by baseline TST surveys) as well as other factors found to differ between study arms at baseline and which may be risk factors for a particular outcome. For the binary outcomes (prevalence, incidence) logistic regression will be used to adjust for confounders at the individual level and cluster level, adopting a two-stage process. The regression model will include terms for the adjustment factors and strata, but not study arm. For each community the fitted model will be used to obtain the ratio of observed (O) to expected (E) or O/E events, and a log transformation applied to this ratio where appropriate. Linear regression of the log mean O/E on strata and arm (2-way ANOVA) will be used to estimate the risk/rate ratio and 95% CI associated with the intervention. The variance for the ratio of mean O/E is calculated from the residual mean square from an ANOVA of O/E on strata and arm.

For the continuous outcomes such as intervention costs and stigma levels, linear regression of the mean number/score will be used to adjust for confounders at the individual level. The regression model will include terms for the adjustment factors and strata, but not study arm. For each community the fitted model will be used to obtain the difference between observed and expected number of events. Linear regression of the difference O-E on strata and arm (2-way ANOVA) will be used to estimate the difference in (O-E) between arms and the 95% CI associated with the intervention. For all analyses, the robustness of the assumptions will be confirmed by a non-parametric stratified permutation test.

Analyses will also look at effects stratified by urban/rural classification, TB notification rates, ART usage, size of community and HIV prevalence. It is recognised that the study has low power to detect differences by subgroup and also the interaction between the interventions (ECF plus HH Vs standard TB/HIV control activities) and so the results of such analyses will be interpreted with caution.

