### Design

#### Study setting

The study is being conducted in Zambia and South Africa, two countries highly affected by the TB and HIV epidemics, and forms part of the CREATE consortium . Study communities have been selected based on TB notification rates greater than 400/100,000 per annum, high HIV seroprevalence and proximity to a TB diagnostic centre. The communities selected are in five provinces of Zambia and in Western Cape province of South Africa and include both urban and rural communities (Fig 1).

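### The 10 degrees of freedom for arm 4 versus arm 1 leave out the four strata that the variance model fits; the 16 for the main comparisons count them

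*Protocol article*

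**What the plan says.** In the Protocol article, under Analytic plan, the variance of the log risk ratio rests on the "residual mean square from a two-way analysis of variance (ANOVA) of community log-risk on stratum and study arm". The next sentence carries that residual into the interval: "A 95% CI for the relative risk/rate will be calculated from this variance". The multiplier named there is the "t-statistic with 16 degrees of freedom (df) for the two main comparisons and 10 df for the comparison of arm 4 Vs arm 1". The same section lists the combined comparison as "ECF plus HH combined (6 Vs 6 communities", in parentheses in the original.

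Under Randomization the strata are defined: "we stratified randomisation by country and the prevalence of TB infection (as measured by baseline TST surveys and categorised as high/low within countries". Under Study setting there are two countries: "The study is being conducted in Zambia and South Africa". Under Sample size: "The total sample size will therefore be 24 communities, 6 in each of the four arms". The error rate to be protected is the two-sided 5% level of that section: "80% power of detecting a significant difference (2-sided p < 0.05".

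The article does not write out the number of strata. It also does not say whether the ANOVA for arm 4 versus arm 1 uses only the 12 communities of those two arms or all 24.

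**The concern.** A t-based interval is valid only if its df match the residual mean square in its standard error. Here the residual comes from a model with strata, but 10 is the df of a plain two-sample comparison of 6 with 6. The neighbouring figure of 16 does make room for the strata, so the two numbers in one sentence follow different rules.

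The interval for the combined package is at stake. The Design section poses its effect as a study question, the Analytic plan names it as one of three comparisons, and the Discussion says that the trial is powered for it. With too many df the interval is too narrow and the test rejects too often. With so few clusters, a difference of three to six df has a visible effect.

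**Working it through.** **Inputs.** 24 communities, 6 per arm (Sample size). 12 communities in arm 4 versus arm 1 (Analytic plan). Strata: 2 countries × 2 tuberculin categories = 4 (Study setting, Randomization). Two-sided level 5%.

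**Reproducing the stated figures.** Residual df = communities − fitted parameters, with S strata.

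- Main comparisons, one mean per stratum-by-arm cell: 24 − 2S. With S = 4 this is 16, as stated, which also supports four strata (S = 3 would give 18, S = 2 would give 20).
- Arm 4 versus arm 1, no strata: 12 − 2 = 10, as stated. A stratified model of 12 communities gives 10 only if S = 1, whether additive (12 − S − 1) or by cell (12 − 2S). That means no stratification.

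**Df that the described model leaves for arm 4 versus arm 1.**

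- 12 communities, additive strata + arm: 12 − 4 − 1 = 7.
- 12 communities, stratum-by-arm cells: 12 − 2×4 = 4.
- 24 communities, additive strata + four-level arm: 24 − 4 − 3 = 17.
- 24 communities, stratum by four-arm cells: 24 − 16 = 8.

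**Consequence of using t(10) = 2.228.** If the residual has v df, the true size is 2·P(T_v > 2.228), and the planned interval has 2.228 / t_v of the correct width.

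| Residual df v | Correct t | Planned / correct width | True size |
|---|---|---|---|
| 7 | 2.365 | 0.94 (6% too narrow) | 6.1% |
| 4 | 2.776 | 0.80 (20% too narrow) | 9.0% |
| 17 | 2.110 | 1.06 (6% too wide) | 4.0% |
| 8 | 2.306 | 0.97 (3% too narrow) | 5.6% |

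A simulation of 6 versus 6 communities (200,000 replicates; stratum splits per arm of 2/2/1/1 and 3/1/1/1, both assumed) gave 6.0–6.2% for 7 df and 9.1% for 4 df. The tabulated sizes depend only on v, not on prevalence, the coefficient of variation or the stratum sizes.

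**Main comparisons.** Additive models leave 24 − 4 − 1 = 19 df (one intervention), 24 − 4 − 2 = 18 (both) or 17 (four-level arm). Using t(16) = 2.120 against these gives a size of 4.7–4.9%; against the cell model it is exact.

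**The case against.** The strongest counter-argument is that the article never says that the residual comes from 12 communities. It speaks of study arm, and the design has four. If one additive ANOVA on all 24 communities supplies the residual, t(10) is conservative. This stands, and it means that the direction of the error is not certain. The 12-community reading is the more natural one, given the 6 versus 6 wording, the separate df for this comparison and 10 = 12 − 2, but it is a reading. It does not rescue the 10: the pooled df would be 17 or 8.

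The comparison might have been meant as unstratified, where 10 is right. Then the variance would not be the stratified residual that the preceding sentence prescribes, so the text would still need correcting.

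The plan also confirms all analyses with a stratified permutation test. That test needs no t df and would expose a distorted p-value, so it is a partial safeguard. It does not correct the reported interval.

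A reader might infer that the trial's type I error is 6–9%, or that the primary results are affected. The documents support neither. The 9% needs a stratum-by-arm model inferred only from the 16, whereas regression on strata and arm, read plainly, is additive. The primary questions are the two 12 versus 12 comparisons, for which 16 df is valid or slightly cautious.

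**Conclusion.** The point holds as an inconsistency: 10 df matches no stratified reading of the Analytic plan, and it follows a different rule from the 16 beside it. The best-supported size is modest: 7 df instead of 10, an interval about 6% too narrow and a size of about 6.1%. This assumes four strata, an additive model and a residual from arms 1 and 4 only. Across the other readings the size runs from about 4.0% (24 communities, additive) to about 9.0% (12 communities, stratum-by-arm), so neither the larger figure nor anti-conservatism as such can be stated as fact. Only the third comparison is affected. It should be fixed, but it does not threaten the primary analysis.

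**What to change.** State the model for arm 4 versus arm 1 and give its own residual df. There are two consistent options:

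- Analyse the 12 communities alone: 7 df with additive strata + arm, or 4 df if stratum-by-arm terms are fitted.
- Fit one model to all 24 communities with four strata and four-level arm, and take the arm 4 versus arm 1 contrast with 17 df. This is the more precise choice: the multiplier falls from 2.365 to 2.110, about 11%. It assumes a common residual variance across the four arms.

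The 16 df for the main comparisons need no correction for validity. For consistency only, align them with the chosen model, for example 18 df if both interventions enter additively.

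The cost is a line or two in the analysis plan. No design feature, sample size or data collection changes.

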### Outcome measurement

#### Baseline assessment of communities

In order to stratify and restrict the randomisation of communities a baseline assessment was conducted by collating information on TB notification rates, TB treatment outcomes, HIV prevalence data and the prevalence of tuberculous infection in school children (see below). In addition to the quantitative baseline assessment, a rapid qualitative appraisal of the communities was conducted. This appraisal involved community mapping, observation and key informant interviews to understand the domains of TB in the local community including population movement, congregation points, beliefs and knowledge about TB and HIV as well as general socio-economic information about the communities

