#### Secondary outcome cohort (SOC)

150 consecutive TB patients and their households are being recruited in each community and asked to complete a baseline questionnaire containing demographic and specific TB and HIV data as well as questions about stigma relating to TB and HIV. Adults are asked to provide a serum sample to test for HIV and both adults and children are tested for TB infection. This cohort will be visited after eighteen months and again after three years of the intervention to allow measurement of HIV incidence, the incidence of TB infection, the incidence of TB disease and changes in perceptions of stigma.

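### For stigma and TB treatment outcomes, the adjusted analysis admits the outcome's own baseline value only if the arms are seen to differ on it; naming it in advance would be a cheap gain in precision

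*Protocol article*

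**What the plan says.** **Baseline data.** In the section Secondary outcome cohort (SOC), patients and their households are "asked to complete a baseline questionnaire containing demographic and specific TB and HIV data as well as questions about stigma relating to TB and HIV". The schedule is: "This cohort will be visited after eighteen months and again after three years of the intervention", with "the incidence of TB disease and changes in perceptions of stigma" among the things to be measured. For TB treatment outcomes, the section Baseline assessment of communities reports that, before allocation, "a baseline assessment was conducted by collating information on TB notification rates, TB treatment outcomes, HIV prevalence data"; skin-test surveys in primary schools formed a further part of it. Both measures are listed as secondary outcomes under Outcome measures.

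**Crude models.** For continuous outcomes the Analytic plan states: "Linear regression of the mean score/number on strata and arm (2-way ANOVA on intervention and strata) will be used to estimate" the difference and its 95% CI. A parallel sentence for binary outcomes regresses the community log risk on strata and arm.

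**Adjusted models.** The Analytic plan then adds adjusted analyses for both types of outcome and mentions stigma by name: "Potential confounding factors will include age, sex, TB infection prevalence (as calculated by baseline TST surveys"), plus other factors on which the arms are found to differ at baseline and that may be risk factors for the outcome. A first model without arm yields observed and expected values for each community. Their ratio or difference is then regressed on strata and arm. Adjustment is described at individual and cluster level for binary outcomes, but only at individual level for continuous ones.

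**Balance by design.** The section Randomization stratifies by country and tuberculin prevalence and restricts on tuberculin prevalence, HIV prevalence, urban/rural, social context and location. It lists neither stigma nor treatment outcomes.

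**The concern.** A community's starting level is often the best single predictor of its later level. The Discussion describes seven languages and many cultures, so lasting differences between communities in stigma are plausible. Programme performance may also differ persistently. In a comparison of 12 with 12 communities, that spread goes straight into the residual that sets the confidence interval.

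The stated rule for extra covariates looks at the wrong property. Imbalance decides whether the baseline value enters, whereas the precision gain depends on how well it predicts the outcome. If the baseline value is balanced, the rule leaves it out and the gain is lost. If it is somewhat unbalanced, entry depends on a judgement made after seeing the arms.

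The household intervention includes psychosocial and adherence support, so these two outcomes bear on how it is meant to work. An imprecise estimate would be a real, though secondary, loss.

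**Working it through.** **Inputs from the protocol article.** 24 communities, compared 12 v 12; community-level regression on strata and arm; t-statistic on 16 df for the two main comparisons and 10 df for arm 4 v arm 1.

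**Assumed input.** r, the within-stratum correlation between a community's baseline and follow-up values. The article gives no figure, so I take 0 to 0.7.

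**The plan's own figure.** The article gives no sample size, power or precision figure for either outcome. Its 24 communities come from the primary outcome. With c = 1 + (1.96 + 0.84)² × [p0(1−p0)/n + p1(1−p1)/n + k²(p0² + p1²)]/(p0−p1)², p0 = 0.01, p1 = 0.007, k = 0.20 and n = 4,000 (5,000 less 20%), 2c = 19.74. Multiplying by 1.2 gives 23.69, that is 24. Nothing below depends on this.

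**Size of chance imbalance.** Before stratification and restriction, the difference in baseline means between two sets of 12 communities has SD √(2/12) = 0.41 community SDs, a 95% range of ±1.96 × 0.41 = ±0.80. Appreciable imbalance is plausible, and so is near balance, in which case the rule leaves the covariate out.

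**Effect of adding the baseline value.** The approximate ratio of CI widths (with baseline value to without) is

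√[(1 − r²)(1 + 1/(df − 2))] × t(df − 1)/t(df).

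At 16 df, √(1 + 1/14) = 1.035 and t(15)/t(16) = 2.131/2.120 = 1.005. The fixed cost is therefore a factor of 1.041, to be multiplied by √(1 − r²). As a check, 24 communities in four equal strata were simulated, 4,000 data sets per r. That layout leaves 24 − 4 − 1 = 19 df rather than 16; equal strata are an assumption.

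| r | √(1 − r²) | Formula, 16 to 15 df | Simulation, 19 to 18 df |
|---|---|---|---|
| 0 | 1.000 | 1.04 | 1.03 |
| 0.2 | 0.980 | 1.02 | 1.01 |
| 0.3 | 0.954 | 0.99 | 0.99 |
| 0.5 | 0.866 | 0.90 | 0.89 |
| 0.7 | 0.714 | 0.74 | 0.74 |

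Break-even is where 1 − r² = 1/1.041² = 0.923, so r = √0.077, about 0.28. In the simulation the true effect was zero and the mean estimate was within 0.02 of zero with and without the covariate: the crude analysis loses precision but is not biased.

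For arm 4 v arm 1 the price is higher. From the stated 10 df the fixed factor is √(1 + 1/8) × t(9)/t(10) = 1.061 × 1.015 = 1.077, so break-even rises to r = √(1 − 1/1.077²), about 0.37.

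These figures treat the baseline value as a covariate in the community-level regression. The article's two-stage version was not simulated separately.

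**The case against.** A reader might infer that the planned models contain only strata and arm, so that chance baseline differences stay in the reported effects. The documents do not support that. The Analytic plan promises adjusted analyses for both outcome types, and a baseline value that differs between arms is the kind of factor its rule would admit. In the crude estimate, chance imbalance adds variance that the confidence interval already covers.

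Other points against the concern also stand, in whole or in part:

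- **The gain is not free.** It costs one degree of freedom, and below r of about 0.28 the interval gets wider. The article gives no r.
- **Baseline and endpoint treatment outcomes may not be the same measure.** The endpoint comes from strengthened registers, and standard practice is to be improved where necessary in all arms. Both can weaken the correlation.
- **The stigma baseline may not precede exposure.** The article does not say that the questionnaire comes before a household's first intervention visit, and enhanced case finding can change who is diagnosed and so who joins the cohort.
- **Balance may be partly achieved.** Restriction on social context and location may capture some of the cultural spread, and the baseline assessment was made in order to inform the allocation. The details are in a paper not shown.
- **Change versus level is not a contradiction.** The cohort section speaks of changes in stigma, but Outcome measures lists stigma levels, and levels are what is analysed.
- **An analysis plan may name the covariates.** The list of adjusters is open, and these are secondary outcomes.

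The last point would dispose of the matter if the article were merely silent. It is not: it states a selection rule, and under that rule a balanced baseline value has no place in the model.

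**Conclusion.** The point holds as a cheap improvement, not as an error that threatens a conclusion. For stigma and TB treatment outcomes, the crude models omit the baseline value and the adjusted models admit it only on observed imbalance. The crude analysis remains valid and unbiased, but less precise than it could be if baseline values predict later ones.

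Whether there is a material gain turns entirely on r. At r = 0.5 or above the interval narrows by at least about a tenth; at 0.2 or below it widens by 1-4%. The case is stronger for stigma, where the same cohort is asked again, provided the first questionnaire precedes exposure. It is least certain for treatment outcomes, because registers and programme practice were strengthened after baseline. The primary outcome, TB prevalence, is not affected.

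**What to change.** In the adjusted analysis, name the community's baseline value of the same outcome as a covariate for these two outcomes, whether or not it differs between arms:

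- **TB treatment outcomes:** the community's pre-randomisation log risk from the baseline assessment, added to the second-stage regression on strata and arm.
- **Stigma:** the community mean baseline score in the second-stage regression, or the household's own baseline score in the first-stage model. Use it where the baseline questionnaire precedes the household's exposure to the intervention. Show the enhanced case finding comparison with and without it, because mobilisation may already have touched the baseline scores.
- **Degrees of freedom:** reduce by one (16 to 15; 10 to 9 for arm 4 v arm 1).
- **Reporting:** keep the crude strata-and-arm result alongside.

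The wording should be fixed before follow-up data are compared by arm. The change needs no measurement beyond those already planned. Its costs are one degree of freedom, a slightly wider interval if r turns out low, and, for stigma, some risk of adjusting away an early effect, which the crude result would reveal.
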